## Methods/design

### Patient selection

In all, 26 patients from the Helsinki University Hospital, Finland, will be recruited to the study in chronological order by the head researcher. Similar to our previous clinical cell therapy trial [28–31], patients of either gender will be initially evaluated for participation by the cardiologists. Patients with heart failure and scheduled for elective CABG are considered eligible for participation in the trial if they meet the inclusion criteria. The criteria for inclusion and exclusion of the patients are presented in Table 1. The first six patients will be recruited to the atrial appendage-derived cell (AADC) arm. Each patient is given both oral and written information about the trial, and the patient’s written informed consent is required for participation and obtained by the head researcher. After scheduling to surgery, patients will undergo a period of at least 4 to 8 weeks for optimization of drug therapy while waiting for the elective operation.

**Table 1 Tab1:** Inclusion and exclusion criteria for patients enrolled in the study

Criteria for eligibilty
Inclusion criteria
1 Stable coronary artery disease filling the criteria for bypass surgery 2 Age between 18 and 75 years 3 Informed consent obtained 4 LVEF between ≤ 45 and ≥ 20% 5 NYHA class II–IV heart failure symptoms
Exclusion criteria
1 Heart failure due to LV outflow tract obstruction 2 History of life-threatening ventricular arrhythmias or resuscitation, a condition possibly repeating, or an implantable cardioverter-defibrillator 3 Stroke or other disabling condition within 3 months before screening 4 Severe valve disease or scheduled valve surgery 5 Renal dysfunction (GFR < 84 ml/min/1.73 m) 6 Other disease limiting life expectancy 7 Contraindications for coronary angiogram or MRI 8 Participation in some other clinical trial

*LVEF* left ventricular ejection fraction, *NYHA* New York Heart Association, *LV* left ventriculum, *GFR* glomerular filtration rate

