Echocardiography (ECHO), quality of life (QoL) questionnaire (standardized SF-36 health survey questionnaire), New York Heart Association (NYHA) class, basic laboratory tests, and N-terminal pro-B-type natriuretic peptide (NT-proBNP) from blood are all evaluated at baseline as well as at 3 and 6 months of the follow-up. Blood RNA and EDTA plasma samples are taken at the pretrial and at 6 months of the follow-up to search markers for prognostic factors. Cardiac MRI is performed at the pretrial and at 6 months of the follow-up.

To determine the safety of the procedure, the next 20 patients who meet the same inclusion and exclusion criteria and are scheduled for elective CABG operation are recruited to the study as control patients. These patients are treated according to the normal hospital protocol, without the extracellular matrix (ECM) sheet and any additional imaging, examination, or blood tests required for the AADC therapy group. Written consent is obtained also from the control patients.

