### Statistical analysis

Statistical methodology as published previously by Pätilä et al. [28] will be utilized. Briefly, the Mann-Whitney *U* test will be used for non-parametric continuous variables and results will be reported as median with interquartile range (IQR). Categorical variables will be analyzed using Fisher’s exact test. Intra-observer variability will be assessed using the Bland-Altman method. Testing for *p* values will be carried out two-sided with *p* < 0.05 considered statistically significant. Results should be treated as preliminary due to the small sample size and will be presented with 95% confidence intervals. A sample size of 26 has been shown to be sufficient in our previous studies to demonstrate safety. Computation will be achieved with PASW Statistics (IBM Inc., Armonk, NY) or equivalent software.

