The purpose of this study is to address patient safety and clinical feasibility of the therapy. We will determine the success of this trial based on the primary outcome measures. If the therapy is proved to be safe without any disturbances in patients’ cardiac rhythm, hemodynamics, and cardiac function and the method can be successfully performed simultaneously with bypass surgery, the results of this trial are then further evaluated in succeeding trials for transplant’s therapeutic efficacy. Double-blind randomization and placebo control using the matrix sheet with and without the micrografts will be considered for our future studies.

Our interests has also been combining stem cell therapy with gene therapy and using autologous minimally manipulated micrografts in conjunction with CABG surgery [47–49]. By administrating genetically modified transplanted cells, we are able to repair also faulty genetic tissue of the heart [47]. Even though cell therapy has promising results, studies regarding safety and clinical efficacy require further investigation.

This study on feasibility and safety of autologous atrial micrograft epicardial transplantation has some limitations. The allocation is not randomized, and the patients are recruited to the groups in chronological order. Also, this trial is carried out as a one-center trial, and therefore, the number of eligible patients is small. Although randomization does not occur, we have considered that no selection bias will take place due to low number of patients and because all patients who are eligible and give their consent are included in the study.

In conclusion, given the severe problems associated with heart failure and its increasing high prevalence [50] in the elderly population, it is of utmost importance to devise effective novel evidence-based cell therapies. Epicardial delivery of AADCs with ECM cells represents a novel approach to restore the cellular loss of infarcted myocardium. We believe that AADC therapy administered during CABG surgery will have impact on patient treatment in the future.

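### The plan claims that 26 patients can demonstrate safety, but its only test of the continuous safety measures is for a difference, and its 95% intervals are not tied to a between-group difference

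*Protocol article*

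**What the plan says.** All references are to the protocol article.

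- **Groups (Patient selection).** "The first six patients will be recruited to the atrial appendage-derived cell (AADC) arm". The controls follow, and their purpose is stated: "To determine the safety of the procedure, the next 20 patients who meet the same inclusion and exclusion criteria".
- **Sample size (Statistical analysis).** "A sample size of 26 has been shown to be sufficient in our previous studies to demonstrate safety". No effect size, SD, margin or power accompanies this.
- **Test (Statistical analysis).** For continuous measures, "the Mann-Whitney *U* test will be used for non-parametric continuous variables and results will be reported as median with interquartile range (IQR"). The decision threshold is "Testing for *p* values will be carried out two-sided with *p* < 0.05 considered statistically significant".
- **Interval and caveat (Statistical analysis).** The next sentence says that results are to be treated as preliminary because the sample is small, and will carry 95% confidence intervals. It does not say which quantity the intervals describe.
- **Success (Discussion).** "We will determine the success of this trial based on the primary outcome measures". The condition for going on to efficacy trials begins "If the therapy is proved to be safe without any disturbances in patients’ cardiac rhythm, hemodynamics, and cardiac function", together with technical success during surgery.

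The continuous primary safety measures in Table 2 are cardiac index, hemoglobin, SvO2, potassium, glucose, left ventricular ejection fraction and pericardial effusion.

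**The concern.** To demonstrate safety against a control group is to claim that treated patients are not materially worse. A Mann-Whitney test takes no difference as its null hypothesis, so it can only produce evidence that a difference exists. Failing to reject is not evidence that harm is absent, and it becomes more likely as the sample shrinks.

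The article pairs this test with wording about demonstrating and proving safety, and gives the reader nothing else by which to judge the continuous measures. The summaries it names are medians and IQRs. If the promised intervals are read as belonging to each group separately, they do not show how much worsening is still compatible with the data.

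The result decides whether efficacy trials follow in patients with reduced cardiac function. A table of non-significant p values from 6 against 20 patients could therefore carry more weight than it can bear.

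**Working it through.** **Inputs from the article.** 6 treated, 20 controls, Mann-Whitney test, two-sided 0.05.

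**Assumptions, because the article gives none.** Size of true harm, from 0.5 to 2 SD; shape of the data, normal or (as a sensitivity case) standardised lognormal with sigma 0.5 shifted upward.

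**1. The plan's own figure.** 6 + 20 = 26 agrees with the stated total. That 26 suffices to demonstrate safety cannot be reproduced, because its only stated basis is the group's earlier studies.

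**2. How often the planned test misses a real worsening.** For 6 v 20 the exact two-sided test rejects when U ≤ 27 or U ≥ 120 − 27 = 93 (true size 0.0459). Non-significant share = 1 − power, from 200,000 simulated trials per row:

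| True worsening | Power, normal | Missed, normal | Missed, skewed |
|---|---|---|---|
| 0.5 SD | 16.0% | 84% | 80% |
| 0.8 SD | 34.3% | 66% | 53% |
| 1.0 SD | 49.7% | 50% | 34% |
| 1.25 SD | 68.3% | 32% | 15% |
| 1.5 SD | 83.2% | 17% | 6% |
| 2.0 SD | 97.3% | 3% | under 1% |

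As a check at 1 SD with normal data, a t test has 54.1% power (46% missed) and the normal approximation gives 57.5% (43% missed).

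**3. What the interval can exclude.** For a mean difference, in SD units:

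half-width = t(0.975, 24 df) × √(1/6 + 1/20) = 2.064 × 0.4655 = 0.961 SD.

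If the observed difference is exactly zero, a worsening of up to about 0.96 SD is not excluded. If the observed worsening is just under 0.96 SD, the corresponding t test is still non-significant, and the interval reaches almost 0.961 + 0.961 = 1.92 SD.

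**4. What an explicit limit would yield.** Illustration only: the true difference is zero and the adverse end of the 95% interval must fall inside an assumed limit (noncentral t, 24 df).

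- Limit 0.5 SD: met in 17.7% of trials, so inconclusive in about 82%.
- Limit 1.0 SD: met in 54.1%, so inconclusive in about 46%.
- Limit 1.5 SD: met in 87.1%, so inconclusive in about 13%.

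These figures are for one measure at a time.

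**The case against.** The strongest reply is that the article nowhere says a p value of 0.05 or more will be read as safety. That is correct. A reader might infer such a rule from the words about demonstrating and proving safety, but the success statement instead speaks of the absence of disturbances in rhythm, hemodynamics and cardiac function. That is a patient-level clinical criterion. The Safety considerations section adds that any abnormality halts the study for evaluation. The supportable statement is that non-significance *could* be taken as safety, because the disturbance criterion is not defined and the p threshold is the only numerical rule given.

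Other parts of the reply also stand:

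- **The article already has some protection.** It promises 95% intervals and calls the results preliminary. This softens the problem. It does not remove it, because the intervals are not tied to a group difference and the claim that 26 suffices to demonstrate safety follows directly after the caveat.
- **A large harm would not usually be missed.** A reader might infer that from the small sample. With normal data the miss rate is about half at 1 SD and 32% at 1.25 SD, and it is lower in the skewed case.
- **Control data may be lacking for some measures.** Controls have no additional imaging, examinations or blood tests required for the treated group. Whether they have echocardiographic ejection fraction or effusion data is not established, so the comparison cannot be presumed for these.
- **A non-inferiority rule is not obligatory.** In a six-patient, non-randomised feasibility study it is a debatable choice, and the absence of a margin is not in itself an error.

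It can also be said that the statistics are given only briefly, with reference to the group's earlier publication, and that the type of interval is detail for a fuller plan. That excuses the missing method. It does not excuse the mismatch, since the test, threshold, sample size and claim of sufficiency all stand in the article.

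**Conclusion.** The point holds in limited form. The article claims more for 26 patients, 6 of them treated, than its written inference can deliver: a test of no difference cannot demonstrate or prove safety. This follows from the logic of the test and does not depend on any assumed effect size.

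The size of the problem does depend on assumptions. With normal data the planned test misses about 84% of 0.5 SD harms and about 50% of 1 SD harms (80% and 34% in the skewed case examined). The interval half-width of about 0.96 SD assumes a common SD and complete data on all 26 patients. The harms in SD units are illustrative and are not the sponsor's figures.

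The documents do not show that the investigators will equate non-significance with safety, or that intervals are absent. The defect is one of wording and reporting that should be corrected, because it changes what the trial may conclude.

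**What to change.** **Statistical analysis section.** For each continuous primary safety measure that controls also have, make the between-group difference (for example the Hodges-Lehmann shift) with its 95% confidence interval the main result. Add wording such as: *A p value of 0.05 or more will not be taken as evidence of safety; the adverse end of the interval shows the worsening that cannot be excluded.* Replace the claim that 26 patients suffice to demonstrate safety with a statement that 26 patients, 6 of them treated, give a preliminary description of safety.

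**Discussion.** Replace the condition that the therapy be proved safe with wording that only worsening outside the interval has been excluded, subject to the stated limitation that allocation is not randomised.

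**Optional.** The clinical team may set a limit of acceptable worsening. Because no masking is described, it should be fixed before any between-group comparison is made. Without a limit, the interval is reported descriptively.

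**Cost.** Wording and one further estimate per measure, with no extra patients or measurements. The real price is in the conclusions: many measures will be reported as inconclusive where they would otherwise have shown no significant difference.

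### The sample-size sentence rests on 26 patients, but only six receive the micrografts, and six cannot exclude clinically important event rates

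*Protocol article*

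**What the plan says.** All of the following is in the protocol article.

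- **Size and allocation (Patient selection).** "In all, 26 patients from the Helsinki University Hospital, Finland, will be recruited to the study in chronological order by the head researcher". Of these, "The first six patients will be recruited to the atrial appendage-derived cell (AADC) arm". For the comparison group, "the next 20 patients who meet the same inclusion and exclusion criteria and are scheduled for elective CABG operation are recruited to the study as" controls, and "These patients are treated according to the normal hospital protocol, without the extracellular matrix (ECM) sheet".
- **Justification (Statistical analysis).** "A sample size of 26 has been shown to be sufficient in our previous studies to demonstrate safety". No event rate, margin, effect size, standard deviation or power accompanies it.
- **Caveat (Statistical analysis, the sentence before).** "Results should be treated as preliminary due to the small sample size and will be presented with 95% confidence intervals".
- **Tests (Statistical analysis).** Mann-Whitney for continuous variables; "Categorical variables will be analyzed using Fisher’s exact test". "Testing for *p* values will be carried out two-sided with *p* < 0.05 considered statistically significant".
- **Use of the result (Discussion).** Success is judged on the primary outcomes, which include safety. Later efficacy trials follow if the therapy has been proved safe, with no disturbance of rhythm, hemodynamics or cardiac function, and can be carried out during bypass surgery.

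**The concern.** The justification counts everyone in the study. Controls supply a background rate, but they say nothing about what happens to a patient who receives the micrografts and sheet. The number that limits any safety statement about the procedure is six.

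The named tests look for differences. With 6 against 20, failing to find one is weak evidence that none exists.

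The sentence also sits badly with its neighbor: the sample is called so small that results are preliminary, and then large enough to show safety. Safety is a primary outcome and progression depends on it. A clean run of six could therefore be reported as establishing safety, with the protocol's own sentence cited in support, while large risks remain compatible with the data.

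**Working it through.** **The plan's own figure.** 6 treated + 20 controls = 26, so the total is consistent. The statement that 26 is enough cannot be reproduced, because no quantity is given to reproduce it from.

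**Step 1: binary outcome, no events among the treated.** Inputs: n = 6 (Patient selection) and 95% confidence (Statistical analysis). With zero events the exact (Clopper-Pearson) upper limit is 1 − 0.025^(1/n) two-sided and 1 − 0.05^(1/n) one-sided.

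| Exposed n | Two-sided 95% upper limit | One-sided 95% upper limit |
|---|---|---|
| 6 (as planned) | 1 − 0.025^(1/6) = 45.9% | 1 − 0.05^(1/6) = 39.3% |
| 26 (if all were exposed) | 1 − 0.025^(1/26) = 13.2% | 1 − 0.05^(1/26) = 10.9% |

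The two-sided limit is 45.9 / 13.2 = about 3.5 times as high with six as with 26. The two-sided figure matches the plan's convention.

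The chance of a clean run in six is (1 − p)^6. It is 0.9^6 = 53% if the true rate is 10%, and 0.8^6 = 26% if it is 20%.

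**Step 2: Fisher's exact test, 6 versus 20.** Two-sided p < 0.05. Power is the total binomial probability of all tables with p < 0.05, by full enumeration. The rates are assumptions.

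| Control rate (assumed) | AADC rate (assumed) | Power |
|---|---|---|
| 5% | 30% | 32% |
| 20% | 40% | 11% |
| 30% | 50% | 8% |

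For about 80% power the AADC rate would have to reach about 61%, 72% or 87% when the control rate is 5%, 10% or 20%.

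In single tables, 2/6 against 1/20 gives p = 0.12 and 3/6 against 2/20 gives p = 0.06. Half of the treated against a tenth of the controls would not be significant.

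**Step 3: continuous outcomes, 6 versus 20.** Exact two-sided Mann-Whitney test, with power by simulation from normal data of equal variance (an assumption). Power is about 50% for a shift of 1 SD, about 78% for 1.4 SD and about 83% for 1.5 SD, so 80% power needs about 1.4 to 1.5 SD.

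**Step 4: which outcomes each step covers.** Table 2 lists nine safety measures. Seven are measured quantities: cardiac index, hemoglobin, mixed venous saturation, potassium, glucose, ejection fraction and effusion in mm. Step 3 applies to these. Need for vasoactive medication and rhythm can be treated as binary, and Steps 1 and 2 apply to them.

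**The case against.** The strongest defense has four parts.

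1. *The claim is about earlier studies.* The sentence reports what the group's previous work showed, and that work is not at hand. A reader might infer that those studies did not show what is claimed; the article gives no basis for saying so. But the limit for six exposed patients does not depend on them. The earlier trial that the Discussion describes injected bone marrow mononuclear cells into the myocardium, which is a different cell product and route.
2. *The article is already cautious.* It calls its results preliminary, plans 95% intervals, lists non-randomized allocation, a single center and few eligible patients as limitations, and leaves efficacy to later trials. This stands and lowers the severity. It does not withdraw the next sentence.
3. *Nothing says that p ≥ 0.05 will be taken as safety.* Correct. A reader might infer such a rule, but the Discussion ties success to the absence of disturbances and not to a test result. The risk is over-reading, which the wording leaves open.
4. *A first feasibility study needs no power calculation.* Agreed, and none is asked for. Six patients can be a reasonable first look. The point is an affirmative claim that the design cannot support.

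Two other strong readings also fail. There is no arithmetic error, since the total adds up and no calculation is shown. And the 46% limit is not a statement about safety as a whole: it holds for a binary outcome with no events, while most of the listed measures are continuous.

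**Conclusion.** The point holds as an unsupported sample-size justification. With six exposed patients the design cannot exclude clinically important event rates: up to 45.9% (two-sided 95%) remains compatible with no events in six. The 6 versus 20 comparisons can reliably detect only very large differences.

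The exact limits need no assumption beyond independent patients with a common risk. The Fisher powers rest on assumed event rates, and the SD figures on normal data with equal variance. Since the caveat and the intervals are already planned and no patient number, test or endpoint needs to change, this is something that should be fixed and not a fatal flaw.

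**What to change.** In Statistical analysis, replace the justification with wording such as:

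> Six patients are exposed. For a binary safety outcome with no events in six, the two-sided 95% upper limit is 46%. The 6 versus 20 comparisons can detect only large differences (about 1.4 to 1.5 SD for continuous measures, assuming normal data). A non-significant difference will not be read as evidence of safety.

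Say that the planned 95% intervals will be given both for the AADC-arm estimate (exact for binary outcomes) and for the AADC-minus-control difference.

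In the Discussion, reword the condition for later trials: in place of the therapy having been proved safe, say that no safety signal was seen, and state which rates the data exclude.

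The cost is wording only, with a less favorable stated claim. No extra patients, tests or measurements are needed.

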### Safety considerations

The patients are monitored, and their cardiac function is closely evaluated under the hospitalization period. In case of any abnormalities, the head researcher will be immediately informed and the study will be halted for evaluation of the cause. Continuation of the study will then be further assessed by the head researcher and the clinical panel responsible for the patient care.

## Discussion

The specific aim of the project is to evaluate safety and feasibility of AADC therapy. Patients enrolled to our study have decreased cardiac function and remodeled left ventricle. Therefore, perioperative safety and adverse effect-free long-term survival are the main concerns regarding the planned procedure and follow-up in our study. The study protocol has been designed keeping also patient convenience in mind. Appendage tissue is harvested during cannulation of the right atrium, and therefore, no additional procedure is needed. Isolation of the cells and preparing the matrix for transplantation is done simultaneously with the CABG operation in the operating room, so the perfusion time and the aorta clamp time are not increased. After the bypass anastomoses, the AADC sheet is placed on the myocardium with three to four sutures allowing the myocardium to contract without interference. Immediately after CABG, the heart is most likely to develop postoperative ischemia due to aorta cross-clamping and following reperfusion. This may change the metabolism of the heart and influence ability of tissues to adapt to the AADC sheet placed on the myocardium. Post-operatively, the patients are closely monitored at the intensive care unit and at the ward in case for any arrhythmias, infection-related decrease in cardiac function, or hemodynamic abnormalities. After the hospitalization period, the patients are followed up at 3 and 6 months for any adverse effects or disturbance in the recovery.

Optimal pharmacotherapy for heart failure and revascularization are crucial, but currently, no medical treatment or surgery can repair the irreversibly infarcted and failing myocardium. Autologous cell therapy offers a way to replace dead cardiac tissue with a viable and functional one. Cell therapies have been demonstrated to be generally safe treatments for heart failure in numerous studies [23, 26, 27]. According to meta-analysis of cell therapy trials, therapies are associated with minimal major intervention-related effects and do not increase the incidence of arrhythmias [37]. The review concluded that cell therapy reduced mortality and re-hospitalization caused by heart failure during long-term follow-up and improved global LVEF, NYHA functional class, proBNP levels, and QoL [37]. On the other hand, some trials reporting results from the myoblast intramyocardial injection have demonstrated increased frequency of arrhythmias compared to epicardial delivery [38–41].

In our previous study, we explored the effects of autologous intramyocardial bone marrow mononuclear cell (BMMC) transplantation in ischemic LV dysfunction [32]. The transplantation was done by injecting autologous BMMCs to the myocardial infarction area intra-operatively. We found no harmful effects of the treatment in any clinically relevant parameters (assessing cardiac function, hemodynamic response, and perioperative myocardial damage) in short- or long-term follow-up [28, 31]. The most important finding in that study was that the BMMC therapy showed significant decrease in the size of local scar on MRI [28], which has been proven to be a major prognostic factor after myocardial infarction [42–44]. The biggest challenge with the method of injecting the cells is the low rate of sustained cells in the graft. This is caused by mechanical leakage [45], poor vascularization of the infarcted area, and apoptosis due to loss of cell anchorage (extracellular matrix) [46]. Compared with the injections, a number of studies have demonstrated that epicardial delivery of the therapeutic cells associates with greater number of retained cells [21] and better graft functionality [22]. Therefore, epicardial delivery of cell-seeded micrografts is the primary choice for the delivery route and the approach in our forthcoming study.

The purpose of this study is to address patient safety and clinical feasibility of the therapy. We will determine the success of this trial based on the primary outcome measures. If the therapy is proved to be safe without any disturbances in patients’ cardiac rhythm, hemodynamics, and cardiac function and the method can be successfully performed simultaneously with bypass surgery, the results of this trial are then further evaluated in succeeding trials for transplant’s therapeutic efficacy. Double-blind randomization and placebo control using the matrix sheet with and without the micrografts will be considered for our future studies.

Our interests has also been combining stem cell therapy with gene therapy and using autologous minimally manipulated micrografts in conjunction with CABG surgery [47–49]. By administrating genetically modified transplanted cells, we are able to repair also faulty genetic tissue of the heart [47]. Even though cell therapy has promising results, studies regarding safety and clinical efficacy require further investigation.

This study on feasibility and safety of autologous atrial micrograft epicardial transplantation has some limitations. The allocation is not randomized, and the patients are recruited to the groups in chronological order. Also, this trial is carried out as a one-center trial, and therefore, the number of eligible patients is small. Although randomization does not occur, we have considered that no selection bias will take place due to low number of patients and because all patients who are eligible and give their consent are included in the study.

In conclusion, given the severe problems associated with heart failure and its increasing high prevalence [50] in the elderly population, it is of utmost importance to devise effective novel evidence-based cell therapies. Epicardial delivery of AADCs with ECM cells represents a novel approach to restore the cellular loss of infarcted myocardium. We believe that AADC therapy administered during CABG surgery will have impact on patient treatment in the future.

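### The Discussion says no selection bias will occur, but the reasons given do not support this: the arms are filled one after the other, under different consents, by a recruiter who can know the arm

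*Protocol article*

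**What the plan says.** **Allocation.** Patient selection gives the order: "In all, 26 patients from the Helsinki University Hospital, Finland, will be recruited to the study in chronological order by the head researcher". It then states: "The first six patients will be recruited to the atrial appendage-derived cell (AADC) arm". The controls follow: "the next 20 patients who meet the same inclusion and exclusion criteria and are scheduled for elective CABG operation are recruited to the study". Their stated purpose is to establish the safety of the procedure.

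**Consent.** In the same section, "the patient’s written informed consent is required for participation and obtained by the head researcher". Control patients also sign, but they are managed under usual hospital care, with no matrix sheet and none of the extra imaging, examinations or blood tests that the AADC arm has.

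**Analysis.** The Statistical analysis section names Mann-Whitney U and Fisher's exact tests, two-sided at 0.05. It calls the results preliminary and gives small sample size as the reason.

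**Limitations.** The Discussion says: "The allocation is not randomized, and the patients are recruited to the groups in chronological order". It then makes this claim: "we have considered that no selection bias will take place due to low number of patients and because all patients who are eligible". The sentence goes on to limit its second reason to those who agree to take part.

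**The concern.** The last statement is categorical and offers two reasons: few patients, and inclusion of everyone eligible who consents. If it were right, a 6 versus 20 difference on a perioperative safety measure could be read as treatment effect plus chance. If it is wrong, such a difference may come from who agreed to take part, or from when they were recruited. The absence of a difference has the same weakness, since a bias in the favourable direction can hide harm.

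This matters because the controls are there for the safety assessment, and the Discussion says that success will be judged on the primary outcomes, with a safe result leading on to efficacy trials. The caveat in the Statistical analysis section covers imprecision only. A reader who accepts the Discussion sentence would have no reason to discount the comparison for selection.

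**Working it through.** The document gives no figure for the size of a bias, so there is none to reproduce. The arm sizes agree with the total: 6 + 20 = 26.

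**Reason 1: low number.** Suppose the two recruitment phases differ by a shift *d* (in SD units) for reasons other than treatment, and treatment has no effect. The expected difference between arm means is *d* at any sample size. Only its standard error depends on the numbers:

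SE = sqrt(1/n1 + 1/n2)

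- 6 versus 20: sqrt(1/6 + 1/20) = sqrt(0.2167) = 0.465 SD
- 60 versus 200: sqrt(1/60 + 1/200) = sqrt(0.02167) = 0.147 SD

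Simulation used normal data and two-sided Mann-Whitney at 0.05 (exact with 20,000 replicates at 6 versus 20; asymptotic with 4,000 replicates at 60 versus 200). The shifts are assumptions.

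| Assumed shift (SD) | Mean spurious difference, 6 v 20 | Mean spurious difference, 60 v 200 | Rejection rate, 6 v 20 |
|---|---|---|---|
| 0 | 0.00 | 0.00 | 4.7% |
| 0.25 | 0.25 | 0.25 | 7.4% |
| 0.5 | 0.50 | 0.50 | 16.2% |
| 0.8 | 0.80 | 0.80 | 34.6% |
| 1.0 | 1.00 | 1.00 | 49.6% |

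A separate simulation at 0.5, 0.8 and 1.0 SD gave 16.8%, 34.3% and 48.8%, hence the ranges 16-17%, 34-35% and 49-50%. The spurious difference is the same in the trial and in one ten times its size, so a low number does not protect against bias.

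Small numbers do add noise. Even a randomised 6:20 split would show a chance imbalance of at least 0.5 SD on a given covariate with probability 2 × [1 − Φ(0.5/0.465)] = 0.28.

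Masking follows from the same table. A true harm of 1.0 SD with an opposite selection shift of 0.5 SD leaves a net 0.5 SD, which is detected in about 16% of trials rather than about 50%. An opposite shift of 1.0 SD would cancel the harm.

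**Reason 2: all eligible consenters are included.** Set side by side, the text of the article shows three ways in which the arms can still differ:

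- *Consent.* The first six agree to an added experimental graft with study MRI and blood sampling. The next 20 agree to take part while receiving usual care. Inclusion depends on consent, and consent is to different things.
- *Knowledge of the arm.* The order is fixed and the head researcher both recruits and obtains consent. The article does not say outright that the arm is known at recruitment, but it follows from these two facts.
- *Calendar time.* Every AADC patient is recruited before every control, so arm and recruitment period cannot be separated.

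**The case against.** **A fairer reading of the low-number reason.** The sentence before last explains that a single centre yields few eligible patients. Read with it, the reason may mean that eligible patients are scarce and all are taken, leaving no room to pick. That has some force: consecutive enrolment under the same criteria does limit picking by the investigator. It does not deal with consent or calendar time.

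**Disclosure.** The article lists non-randomised, chronological allocation as a limitation, calls its results preliminary and says that randomisation will be considered for later studies. This stands, so the main weakness is not hidden. The defect is the sentence that then denies its consequence.

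**Stronger readings that the document does not support.** A reader might infer that patients who refuse the graft can never become controls, that controls consent only to the use of routine data, or that surgeons, drugs or intensive care practice changed between phases. None of these is stated. Nor does sequential recruitment mean that operation dates cannot overlap, since patients wait at least 4 to 8 weeks for drug optimisation before surgery. The shifts in the table are not estimates for this trial either, and at the small end (0.25 SD) the inflation is modest.

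**Randomisation.** A reader might also conclude that the trial has to be randomised. Recruitment began in February 2016 according to Trial status, and treating the first six patients is a defensible choice in a small first feasibility study. Screening counts and baseline tables are commonly left to a full protocol or analysis plan, so their absence from the article is not itself a fault.

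**Conclusion.** The statement is wrong as written. Neither reason rules out selection bias: one concerns precision, and the other restricts only one route by which bias can enter. Selection bias through arm-specific consent, and bias from the non-concurrent recruitment periods, both remain possible.

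How large the bias is, and in which direction, cannot be said from the document. The rejection rates of roughly 7% to 50% against a nominal 5% rest on normal data, no treatment effect and assumed shifts of 0.25 to 1.0 SD. They show what is possible, not what is expected.

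The reach is limited. The AADC-versus-control safety comparison is affected. The four feasibility outcomes concern making and delivering the graft and have no control counterpart, and the 6-month MRI change is within the AADC arm because controls have no additional imaging.

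**What to change.** 1. Replace the Discussion sentence with a statement that controls are recruited non-concurrently and consent to something different, so that selection and calendar-time bias are possible.
2. Treat between-arm p-values on the safety measures as descriptive. Do not attribute a difference, or the absence of one, to the treatment.
3. To support that reading, report eligible, declined and enrolled counts, and baseline characteristics such as age, LVEF and NYHA class, by arm.

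Concurrent or randomised allocation is optional and not part of this change. The cost is some rewording, one extra table and a weaker stated safety conclusion. The 26 patients and the conduct of the trial stay as they are.
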